#### **5.2.3 Inclusion Criteria for HIV-uninfected volunteers**

1. Healthy male or female, as assessed by a medical history and physical exam
2. At least 18 years of age on the day of screening and not older than 49 years on the day of randomization;

3. Willing to comply with the requirements of the protocol and available for follow-up for the planned duration of the study;
4. In the opinion of the Principal Investigator or designee, has understood the information provided and has provided written informed consent before any study-related procedures are performed;
5. Willing to undergo couple HIV testing, STI screening, HIV counseling and receive test results, and share results with partner
6. At risk for HIV infection as defined by at least one of the following: HIV-infected partner not using ART in the past 3 months and had episodes of unprotected vaginal sex with partner in the past 3 months
7. If a female of childbearing potential (i.e., not post-menopausal or surgically sterile), using an effective method of non-barrier contraception (hormonal contraceptive; intrauterine device (IUD); surgical sterility) from 7 days prior to randomization until the end of the study. All female volunteers must be willing to undergo urine pregnancy tests at time points as indicated in the Schedule of Procedures (Appendix A1).
8. HIV-infected partner is willing and eligible (see 5.2.5. and 5.2.6.) to enrol in the study

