#### **14.2.6 HIV risk behaviour change**

HIV risk behaviour will be measured at each visit by the number of steady and casual partners reported in the previous month, frequency of unprotected sex acts, and substance use prior to or during sex. Methods for repeated measurements, such as linear mixed effects models, will be applied to these data to assess both individual and group level changes in HIV risk behaviour. These models will incorporate time on and off study treatment.

Assuming condoms are used always or frequently by 60% of volunteers at baseline, this study has 85% power to detect a decrease in condom usage by treatment group (n=24) if volunteers reduce the rate to 30%. A decrease to a rate of 40% would be detected with 49% power. Power is based on a two-sided, 0.05 level test of a binomial proportion.

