| Pre-/Post HIV-test counselling                                                                                                                                                                                                                       | X      | X     |     |     | X     |            | X      | X     | X         | X     | X**         | X**       |           |
| HIV risk reduction counselling / Family planning counselling                                                                                                                                                                                         | X      | X     |     |     | X     |            | X      | X     |           | X***  | X           | X         |           |
| Adherence counselling                                                                                                                                                                                                                                |        | X     | X   | X   | X     |            | X      | X     |           |       |             |           |           |
| Follow-back interview (adherence, sexual risk behaviour, medication sharing)                                                                                                                                                                         |        |       | X   | X   | X     |            | X      | X     | X         |       |             |           |           |
| Acceptability assessment (focus group/individual interview)                                                                                                                                                                                          |        |       |     |     |       |            |        |       | X*        |       |             |           |           |
| IVR or SMS behavioural assessment                                                                                                                                                                                                                    |        | Daily |     |     |       |            |        |       |           |       |             |           |           |

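### The 85% and 49% power for a fall in condom use treat the 60% baseline as a known constant, and no follow-back interview is scheduled at week 0 or week 24 to support the planned on/off-treatment model.

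*Protocol*

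**What the plan says.** Change in HIV risk behaviour is a primary objective (section 4.1), with behavioural primary endpoints in section 5.1.1. Section 14.2.6 sets the starting point: "Assuming condoms are used always or frequently by 60% of volunteers at baseline". It then states that "this study has 85% power to detect a decrease in condom usage by treatment group (n=24) if volunteers reduce the rate to 30" per cent, and adds: "A decrease to a rate of 40% would be detected with 49% power". The test named is a two-sided 5% test of a single binomial proportion. The synopsis repeats both figures.

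The same section says risk behaviour is measured at every visit and that repeated-measures models, for example linear mixed models, will assess individual and group change. It adds: "These models will incorporate time on and off study treatment".

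The Appendix A1 row headed "Follow-back interview (adherence, sexual risk behaviour, medication sharing") is marked at W1, W2, W4, W8, W12 and W16/ET. It is not marked at week 0 or W24. Week 0 has a separate HIV risk assessment (also listed in section 6.2), which appears at that visit only. Drug stops at week 16. Section 6.7 describes W24 as HIV testing, blood collection and counselling.

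**The concern.** A one-sample test asks whether the follow-up proportion differs from a number fixed in advance. Section 14.2.6 asks whether these volunteers have moved from where they started. Their baseline is estimated from the same 24 people, so it has sampling error, and some volunteers may move up while others move down. The one-sample calculation ignores both.

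The protocol itself raises risk compensation as a potential harm (section 3.6). If the paired power is well below 85%, a finding of no change is weaker reassurance than the stated figure suggests.

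The schedule problem is separate. A model with an off-treatment period needs behaviour data from that period, and a before/after comparison is cleanest when both ends use the same instrument. The follow-back interview is scheduled at neither end.

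**Working it through.** **Inputs.** From section 14.2.6: n = 24 per group, baseline 0.60, follow-up 0.30 or 0.40, two-sided alpha 0.05. The within-person correlation (rho) between baseline and follow-up is not given. It is an assumption here, varied from 0 to the largest feasible value.

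**Reproducing the stated power.** Under X ~ Bin(24, 0.60), the exact two-sided test rejects at X ≤ 9 (tail probability 0.0217) or X ≥ 20 (0.0134).

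- Follow-up 0.30: P(reject) = 0.847, stated as 85%.
- Follow-up 0.40: P(reject) = 0.489, stated as 49%.

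Both match, so 60% was entered as a known constant.

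**Paired power.** Let p0 be the baseline and p1 the follow-up proportion. The proportion using condoms frequently at both times is

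p11 = p0·p1 + rho·√[p0(1−p0)·p1(1−p1)].

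Downward switchers are p10 = p0 − p11 and upward switchers are p01 = p1 − p11. The largest feasible rho has p01 = 0:

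- 60% to 30%: (0.30 − 0.18)/√(0.24 × 0.21) = 0.53.
- 60% to 40%: (0.40 − 0.24)/0.24 = 0.67.

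Example, 60% to 30% at rho = 0.4: p11 = 0.18 + 0.4 × 0.2245 = 0.270, so p10 = 0.330 and p01 = 0.030.

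Power is the multinomial probability, over all splits of 24 pairs into b downward, c upward and the rest unchanged, of rejecting with b > c. With m = b + c:

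- exact: 2·P(Bin(m, 0.5) ≤ min(b, c)) ≤ 0.05;
- mid-p: the same p-value less P(Bin(m, 0.5) = min(b, c));
- asymptotic: (b − c)²/m > 3.84.

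60% to 30% (stated 85%):

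| rho | p10 | p01 | exact | mid-p | asymptotic |
|---|---|---|---|---|---|
| 0 | 0.420 | 0.120 | 42.4% | 52.0% | 52.0% |
| 0.2 | 0.375 | 0.075 | 50.9% | 61.1% | 61.3% |
| 0.3 | 0.353 | 0.053 | 56.8% | 67.5% | 68.0% |
| 0.4 | 0.330 | 0.030 | 64.1% | 75.3% | 77.0% |
| 0.5 | 0.308 | 0.008 | 73.3% | 85.0% | 89.8% |
| max (0.53) | 0.300 | 0 | 77.1% | 88.9% | 95.8% |

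60% to 40% (stated 49%):

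| rho | p10 | p01 | exact | mid-p | asymptotic |
|---|---|---|---|---|---|
| 0 | 0.360 | 0.160 | 18.4% | 25.4% | 25.4% |
| 0.2 | 0.312 | 0.112 | 21.8% | 30.0% | 30.1% |
| 0.3 | 0.288 | 0.088 | 24.0% | 33.3% | 33.9% |
| 0.4 | 0.264 | 0.064 | 26.7% | 37.5% | 39.3% |
| 0.5 | 0.240 | 0.040 | 29.6% | 42.7% | 47.6% |
| 0.6 | 0.216 | 0.016 | 32.6% | 49.0% | 60.8% |
| max (0.67) | 0.200 | 0 | 34.4% | 54.0% | 73.6% |

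**Schedule, side by side.**

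| Section 14.2.6 needs | Appendix A1 and sections 6.2, 6.7 provide |
|---|---|
| Baseline behaviour | HIV risk assessment at week 0, a separate instrument; no follow-back interview |
| Behaviour on drug | Follow-back interview at W1, W2, W4, W8, W12, W16/ET |
| Behaviour off drug | W24 only; no behaviour interview listed |

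**The case against.** The strongest reply is that nothing was miscalculated. The test is named and the figures are right for it. That stands: the fault is a mismatch between the test and the question, not an arithmetic error.

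A reader might infer that true power is far below 85% whatever is assumed. The documents do not support that. The loss depends on a correlation and a test version that the protocol does not give. For 60% to 30%, mid-p reaches 85.0% and the asymptotic test 89.8% at a correlation of 0.5. That does require fewer than 1% of volunteers to move up to frequent condom use, although section 7.4 provides counselling and free condoms at every visit.

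McNemar's test is also not the planned analysis. A repeated-measures model over several interviews may recover some power; this was not computed. The synopsis speaks of describing behaviour change with descriptive statistics, so it is not certain that a null result would be presented as an 85%-powered one.

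On the schedule, a reader might infer that there is no baseline and no off-drug behaviour information at all. That goes too far. A risk assessment exists at week 0, and its items may overlap with the interview. Daily IVR/SMS (section 9.5) asks about condom use and is marked from randomization; the available text does not show when it ends. Volunteers who stop drug early but stay in follow-up could also give some off-drug interviews. None of this places a follow-back interview at week 0 or W24. The example IVR/SMS questions also omit substance use and the number of casual partners.

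A reader might further suspect regression to the mean, because eligibility asks that volunteers "had episodes of unprotected vaginal sex with partner in the past 3 months", or contamination of the W1 and W2 recall by pre-randomization days. The documents give no basis for sizing the first, and the criterion applies equally to every arm. The interview's day-by-day calendar lets days be split at randomization. Neither is part of this point.

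**Conclusion.** The point holds in two limited parts.

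First, the stated powers answer a one-sample question against a fixed 60%, while the section claims power to detect a fall from the volunteers' own baseline. With 24 pairs and an assumed correlation of 0 to 0.4, power for 60% to 30% is 42-64% (exact) or 52-77% (asymptotic), against 85%. For 60% to 40% it is 18-27% or 25-39%, against 49%. At about 0.5 or above, the mid-p and asymptotic tests reach the stated figures (for the smaller fall, mid-p needs about 0.6). The exact test stays below them at every feasible correlation. These sizes rest on the assumed correlation and on a single before/after pair per volunteer.

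Second, and without any assumption, the schedule does not match the analysis text. The follow-back interview is absent at week 0 and W24, contrary to measurement at every visit, and the off-treatment part of the model has no planned interview data.

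**What to change.** In section 14.2.6 and the synopsis, either restate the figures as paired power over a stated range of within-person correlation, naming the test, or keep 85% and 49% and label them as power against a fixed external 60%. If a paired range is given, use the same correlation span for both falls.

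In Appendix A1 and sections 6.2 and 6.7, add the sexual-behaviour part of the follow-back interview, covering the prior 30 days, at the randomization and W24 visits.

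The cost is a less favourable power statement and two short interviews per volunteer at visits that already take place.

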#### **14.2.7 Medication sharing**

Medicine sharing will be assessed by follow-back interview. Medicine sharing between members of discordant couples will also be assessed by drug levels in the HIV-infected partner

Drug levels in hair samples of study volunteers assigned to FTC/TDF groups will be evaluated for exploratory purposes only.

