|                         | 
Acceptability:
 

• The proportion of volunteers who report willingness to use the study regimen

• The acceptability to the HIV-infected partner of their partner using the investigational product

 
Intracellular drug concentrations:
 

• The mean intracellular drug concentration for each group assigned to FTC/TDF

 
Adherence:
 

• The proportion of volunteers who took, by MEMS (Medication event monitoring system) data, at least 80% of expected doses of the investigational product

• The proportion of volunteers assigned to FTC/TDF who have detectable drug plasma levels within 48 hours of reported use.

• The relationship between intracellular drug levels and adherence in volunteers assigned to FTC/TDF

 
Behavioral:
 

• Reported number of steady and casual sex partners

• Frequency of unprotected vaginal intercourse

• Substance use prior to or during sex

 
Other:
 

• The proportion of volunteers who report somewhat high or high levels of burden in using electronic medication monitoring to measure adherence, and using cell phone communication to measure sexual activity

• The proportion of study days with missing sexual activity data

• The proportion of volunteers who report sharing medications

• The proportion of volunteers assigned to placebo who have detectable intracellular drug levels

• The proportion of HIV-infected partners in discordant couples not on ART with detectable drug levels

• The proportion of volunteers with HIV-specific immune responses as measured by analysis of cellular or humoral immune response, or changes in gene regulation as measured by microarray or proteomic techniques

 |                         |                |                         |         |       |    |         |              |    |         |       |    |         |              |    |

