**5.1.2 Other Endpoints**

- The proportion of volunteers who report somewhat high or high levels of burden in using electronic medication monitoring to measure adherence, and IVR or SMS to measure sexual activity
- The proportion of study days with missing sexual activity data
- The proportion of volunteers who report sharing study medication.
- The proportion of volunteers assigned to placebo that have detectable intracellular drug levels
- The proportion of volunteers with HIV-specific immune responses as measured by analysis of cellular or humoral immune response, or changes in gene regulation as measured by microarray or proteomic techniques

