**5.2.6 Exclusion Criteria for HIV-1 infected partner:**

1. Current use of antiretroviral therapy
2. Concurrent enrolment in another HIV treatment trial

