### **6.9.3 Post-randomization Visits and Final Visit/Early Termination visit**

The HIV-infected partner will be asked to return to the clinic on the days as specified in Appendix A2.

The following procedures will be conducted at these visits as indicated in the Schedule of Procedures (Appendix A2):

- Collection of blood specimen to determine drug levels
- Collection of acceptability information

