## 9.6 Medication Sharing Assessments

Potential for medication sharing will be assessed through the follow-back interview at the time points indicated in Appendix A1.

In discordant couples, it will also be assessed by retrospective intracellular drug levels on HIV-infected partners of volunteers assigned to FTC/TDF. Blood specimens from the HIV-infected partner will be stored at 2 visits. A subset of these samples will be tested retrospectively for drug levels.

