## APPENDIX A2: SCHEDULE OF PROCEDURES FOR HIV-INFECTED PARTNERS

|                                          | Screen | Rando |           |           |           | Final visit/ET |
|------------------------------------------|--------|-------|-----------|-----------|-----------|----------------|
| Study Week                               |        | 0     | W4        | W8        | W12       | W16            |
| Visit Windows (Days)                     |        | -42   | -7/
+2 | -7/
+2 | -7/
+2 | -7/
+2      |
| Drug level testing                       |        |       |           | X         |           | X              |
| Acceptability assessment (questionnaire) |        |       |           |           | X         | X              |
| Informed Consent                         | X      | X     |           |           |           |                |
| Screening Questionnaire                  | X      |       |           |           |           |                |

ET = Early Termination

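### The partner drug-level measure of pill sharing needs the partner's ART status at the draw, but the protocol schedules no record of it after screening

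*Protocol*

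**What the plan says.** The synopsis lists, among the other endpoints, "The proportion of HIV-infected partners in discordant couples not on ART with detectable drug levels". Section 5.1.2, the matching list in the body, has only the self-report endpoint on sharing: "The proportion of volunteers who report sharing study medication".

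Section 9.6 names the follow-back interview first and then, for couples, adds that "it will also be assessed by retrospective intracellular drug levels on HIV-infected partners of volunteers assigned to FTC/TDF". Partner blood is stored at two visits, and "A subset of these samples will be tested retrospectively for drug levels". Section 14.2.7 repeats the two sources: the interview, and then "Medicine sharing between members of discordant couples will also be assessed by drug levels in the HIV-infected partner". Neither section conditions on the partner's own treatment.

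Partner ART is restricted at entry: section 5.2.6 excludes "Current use of antiretroviral therapy". After randomization, section 6.9.3 lists two partner procedures: "Collection of blood specimen to determine drug levels", and acceptability information. Appendix A2 places the blood at weeks 8 and 16, the acceptability questionnaire at weeks 12 and 16, and the screening questionnaire at screening only.

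**The concern.** TDF and FTC are themselves HIV treatment drugs (section 3.3.1), and the partners are HIV-infected adults who are untreated at entry. If a partner starts a regimen containing either drug during follow-up, the assay finds the same substances that a shared study tablet would leave. The drug level alone cannot tell the two apart; only the partner's ART history at the time of the draw can.

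The synopsis restriction shows that the sponsor saw this. Applying it needs ART status at weeks 8 and 16, and no scheduled procedure supplies that. The only status the protocol secures is the one at entry, when every partner is off ART by design. A later starter would then stay in the denominator and could count as detectable. The partner drug level is the objective check on self-reported sharing, and true sharing may be rare, so one or two such samples could change how it is read.

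**Working it through.** The protocol gives no rate, power or sample size for this endpoint, so there is no figure to reproduce. The check is mainly textual.

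**What the endpoint needs against what is scheduled**

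- *Needed (synopsis):* whether each partner is on ART when the sample is drawn, at week 8 or week 16.
- *Screening:* ART is an exclusion (5.2.6), and a screening questionnaire is given. Screening may precede randomization by up to 42 days, which is 6 weeks, so this information can be 6 + 16 = 22 weeks old at the week 16 sample.
- *Randomization (6.9.2):* questions answered and consent reviewed; no medication item.
- *Weeks 8 to 16 (6.9.3, Appendix A2):* blood and acceptability only.
- *Concomitant medications (9.1.2):* solicited from study volunteers and scheduled in Appendix A1, which covers the HIV-uninfected member. Appendix A2 has no such row.
- *A partner who starts ART:* no rule is given.
- *Background control:* section 9.6 tests only partners of FTC/TDF volunteers, so placebo couples cannot show how often drug is detected because of ART.

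**Size, for illustration only**

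From the protocol: 24 + 24 = 48 couples with an FTC/TDF volunteer, and a 16-week period. Assumed, because the protocol gives no value: 10% to 30% of partners start ART per year, and 30% to 70% of those regimens contain TDF or FTC.

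Proportion starting ART within 16 weeks = 1 − exp(−rate × 16/52):

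- Low: 1 − exp(−0.10 × 16/52) = 3.0%
- High: 1 − exp(−0.30 × 16/52) = 8.8%

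Expected partners with drug from their own ART, if all 48 are tested:

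- Low: 48 × 3.0% × 0.3 = 0.4
- High: 48 × 8.8% × 0.7 = 3.0

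Section 9.6 tests only a subset of unstated size. If half the partners were tested, for example, the counts would halve to about 0.2 and 1.5. If the subset is chosen without regard to ART, the expected proportion does not change.

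For comparison, suppose true sharing is 1 or 2 of 48 couples (2% to 4%, also assumed). The low figure of 0.4 lies below that; the high figure of 3.0 exceeds it.

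**The case against.** The best counter-argument is that the sponsor had already recognised the problem. The synopsis excludes partners on ART, ART is an exclusion at entry, and volunteer inclusion criterion 6 refers to a partner without ART in the past 3 months. A reader might infer that any partner who starts ART will be counted as a sharer. The documents do not support that: under the synopsis definition such a partner is outside the endpoint. What stands is narrower, namely that nothing scheduled shows which partners those are.

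A reader might also infer that partner ART is certainly never recorded. That goes too far as well. The items of the partner questionnaire are not shown. Section 6.9.1 uses the word volunteer for partners, so 9.1.2 could be stretched to cover them. Sections 3.7 and 5.2.7 describe a parent cohort with quarterly follow-up in which ART might be noted. But 6.9.3 and Appendix A2 contain no such item, and the protocol does not link cohort records to this endpoint.

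Classification of positive samples and the choice of denominator are commonly left to the analysis plan. That is fair for the analysis wording, but no analysis plan can recover an ART history that was not collected.

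Finally, sharing is not a primary objective. It is described without a test, and the interview is the first-listed measure. That stands and limits the weight of the point.

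**Conclusion.** The gap is real but modest. The synopsis and the body disagree on whether the partner drug-level endpoint exists and on whether it is restricted by ART, and the data needed to apply the restriction at the draw are not scheduled. A false signal requires that a partner starts ART containing TDF or FTC before a sample, and that this sample falls in the tested subset.

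The size is unknown. The range of about 0.4 to 3 of 48 partners rests wholly on assumed rates and on testing everyone. A stronger reading, that the couple-level result would be wholly due to prescribed ART and lead to a wrong conclusion about sharing, is not supported: it would need every positive to come from ART and the interview to be ignored. No primary endpoint is touched. This is a cheap improvement, worth making because the missing history may be hard to reconstruct once samples are assayed retrospectively.

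**What to change.** 1. In 6.9.3 and Appendix A2, add one item to the partner questionnaire at weeks 12 and 16: any ART since the last visit, drug names and start date. The start date given at week 12 covers the week 8 sample retrospectively. Alternatively, ask a brief item at week 8. No questionnaire is scheduled then, but section 6.9 already has partners attend that visit.
2. Restore the partner drug-level endpoint to 5.1.2 with the synopsis restriction to partners not on ART.
3. In 9.6 and 14.2.7, base the sharing proportion on samples from partners not on TDF- or FTC-containing ART at the draw, and report the other samples separately. This condition and the synopsis wording differ only for a partner on ART without either drug; recording drug names allows that case to be settled and stated.

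The cost is one added question, wording changes in five places, and a few samples leaving the denominator.
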